## 9.6. SAFETY MONITORING AND REPORTING

### 9.6.1. Cardiac Monitoring

To assess the impact of monthly dosing with DP on QTc prolongation, a sub-group of 66 children (33 in each arm) will be selected to participate in cardiac monitoring sub-study at the beginning of the trial using convenience sampling. Separate written informed consent will be sought for inclusion in this sub-study.

A baseline ECGs will be done prior to the start of the first dose of the first course of DP at 2 weeks post-discharge, and again 2 days later, 4-6 hours after the 3rd dose of DP, and before each

subsequent first dose and after each subsequent 3rd dose of each next course (i.e. about 6 ECGs assessments in total per child). Each ECG will be taken in triplicate. Information on food intake and co-medication will be collected by questionnaire. A 200 micro litre blood sample will be taken for piperazine drug levels at the same time that the ECGs are taken. Piperazine levels will be measured in a specialised laboratory from the Mahidol Oxford Tropical Medicine Research Unit (MORU), in Bangkok, Thailand which is one of the few laboratories globally that have this capacity.

ECGs will be read on site by trained local staff, and forwarded electronically to Makerere University and KEMRI Kisumu for quality control. All abnormal ECGs (see grading below) and a sub-set of other ECGs will be read by a Paediatric Cardiologist fellow. QT intervals will be adjusted for heart rate prior to subsequent analysis using the Fridericia formula ( $QT_c = QT \text{ times the cube-root of the RR interval on the ECG}$ ).

All ECGs will be graded based on the  $QT_c$  interval as mild, moderate, severe and potentially life threatening as per international guidelines from the National Institute of Health (NIH): Division of AIDS (DAIDS) Table for Grading the Severity of Adult and Pediatric Adverse Events.

- Grade 1 (mild): Asymptomatic,  $QT_c$  interval 450 –470 ms
- Grade 2 (moderate): Asymptomatic,  $QT_c$  interval 470-500 ms
- Grade 3 (severe): Asymptomatic,  $QT_c$  interval >500 ms OR  $\geq 60$  ms above baseline (pre-course level)
- Grade 4 (potentially life threatening): Life-threatening consequences, e.g. Torsade de pointes or other associated serious ventricular dysrhythmias

For all children with  $QT_c \geq 450$  ms a repeat ECG will be performed within 30 minutes. Children with confirmed baseline  $QT_c \geq 450$  ms will be excluded from the main trial. If  $QT_c$  value  $\geq 450$  ms are found during follow-up ECGs, the ECG will also be repeated within 30 min. If findings are confirmed the next dose of DP or placebo will be withheld and the local study medical officer notified. In all cases with a confirmed grade 2-4 ECG abnormality, the next course of DP will also continue to be withheld. The decision to stop or continue the DP/Placebo in these children will be made in consultation with the DMEC. This will be reported as an SAE to the ethics committees.

At completion of the Cardiac monitoring study an analysis will be performed by an independent statistician, blinded for the treatment allocation. The statistician will report to the independent DMEC. The DMEC will have a meeting during which they will have access to the unblinded data. The following approach will be taken in terms of stopping rules:

- If there is no evidence of a clinically relevant increase in  $QT_c$  prolongation when comparing the  $QT_c$  prolongation observed after the 3rd dose of the first course (relative to baseline), and after the 3rd dose of the 3 course (as per the previous trial in children 6 to 24 of age in Uganda), they will inform the Trial Steering Committee (TSC) for the study to continue as per the approved protocol. The ethics committees will be informed.
- If there is evidence that the  $QT_c$  prolongation increases with each course, the DMEC will share the results of the interim-analysis with the Trial Steering Committee (TSC) in a joint meeting. The TSC decides on the continuation of the trial and if needed can suggest amendments to the protocol, including screening for  $QT_c$  prolongation in all remaining children in the trial, and/or recommend alternative strategies for PMC, e.g. 6-weekly instead

of monthly DP, or use of alternative drugs. The results and any amendments to the protocol will be submitted to the ethics committees for approval.

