One trial in children 6m to 24m of age in Uganda, included monthly DP for up to 18 monthly courses. As part of this trial detailed sub-studies of the effect of DP on cardiac repolarization were conducted in 26 children. A total of 183 ECGs were conducted; all of the follow-up ECGs had a QTc < 450msec with a mean QTc = 396msec (range 278-444, SD 31.3). There were no differences in the mean (SD) QTc intervals measured 4-6 hours after the 3rd dose (i.e. peak piperaquine levels) for children who had been prescribed 3-5, 6-10, or 11-18 prior doses of DP: Mean (SD)QTc 405 (26), 388 (33) and 396 (33), respectively. Thus this nested cardiac monitoring study shows that monthly courses of DP is not associated with a trend toward increasing QTc prolongation with increasing number of DP courses. DP also provided superior efficacy compared to placebo or comparators in preventing any parasitaemia in participants (pooled Incidence Rate Ratio 0.22 (95% confidence interval 0.11-0.33)). These limited data on repeat DP exposures suggest that repeat 3-day courses of DP given at monthly intervals over 3 month may be safe and effective and a good option for IPT.

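### Section 9.6.1 names the Fridericia QT correction but writes it upside down (QT multiplied, not divided, by the cube root of RR); if applied as written, the 450/470/500 ms limits would almost never be reached

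*Protocol*

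**What the plan says.** Section 9.6.1 (Cardiac Monitoring) states that "QT intervals will be adjusted for heart rate prior to subsequent analysis using the Fridericia formula". The bracket that follows spells the formula out as QT "times the cube-root of the RR interval on the ECG". No unit is given for RR, and the formula appears nowhere else in the protocol.

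The same section grades each ECG on the resulting QTc:
- grade 1: "interval 450 –470 ms";
- grade 2: "interval 470-500 ms";
- grade 3: "interval >500 ms OR" a rise of at least 60 "ms above baseline (pre-course level");
- grade 4: life-threatening consequences.

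A confirmed baseline value of 450 ms or more excludes the child from the main trial. For a value of 450 ms or more at follow-up the rule is: "If findings are confirmed the next dose of DP or placebo will be withheld and the local study medical officer notified". Section 8.5.4 uses QTc for discontinuation in the sub-study, and section 8.6.4 lists QTc prolongation as a safety outcome. At the end of the sub-study the DMEC compares prolongation after the first and third courses, and the TSC may act on the result.

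For reference, section 8.5.2.5 reports an earlier study in Ugandan children in which "all of the follow-up ECGs had a QTc < 450msec with a mean QTc = 396msec" (SD 31.3, range 278 to 444).

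**The concern.** The name and the bracket contradict each other. A rate correction has to cancel the dependence of QT on RR. The cube-root correction takes QT to vary with RR^(1/3), so QT must be divided by that quantity. If it is multiplied, the result varies with RR^(2/3), which doubles the exponent that was meant to disappear. Whenever heart rate is above 60 bpm, RR is below 1 s. QT is then already short and is shortened again.

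QTc is not only reported at the end. It decides on the day whether an ECG is repeated, how it is graded and whether the next dose is withheld, and later it informs whether the trial continues. A value that is systematically low would make abnormal ECGs look normal. Section 9.6.1 sends all abnormal ECGs, but only a subset of the others, to the paediatric cardiology reader. A low value would therefore also remove most of that second look.

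**Working it through.** **Inputs from the protocol.** The formula as written, the 450/470/500 ms and 60 ms limits (section 9.6.1), the reference mean of 396 ms and SD of 31.3 (section 8.5.2.5), and the sub-study design of a 20 ms difference, SD 31, 90% power and two-sided 0.05 (section 8.8.2).

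**Assumptions.** The protocol gives no heart rates, so 80 to 160 bpm is assumed, with 120 as the central value. RR is taken in seconds. The reference values are treated as being on the Fridericia scale.

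**The plan's own figure.** n = (31 × (1.960 + 1.282) / 20)² = 25.2, rounded up to 26. Then 26 / 0.80 = 32.5, rounded up to 33 per arm. The sample size reproduces and is not affected by this point.

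**Ratio of written to Fridericia value.**
- Fridericia: F = QT / RR^(1/3), so QT = F × RR^(1/3).
- As written: W = QT × RR^(1/3) = F × RR^(2/3), with RR = 60 / heart rate.

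| Heart rate (bpm) | RR (s) | W/F | 396 ms recorded as | 500 ms recorded as | F needed for W = 450 ms | 60 ms rise recorded as |
|---|---|---|---|---|---|---|
| 80 | 0.750 | 0.83 | 327 | 413 | 545 | 50 |
| 100 | 0.600 | 0.71 | 282 | 356 | 633 | 43 |
| 120 | 0.500 | 0.63 | 249 | 315 | 714 | 38 |
| 140 | 0.429 | 0.57 | 225 | 284 | 792 | 34 |
| 160 | 0.375 | 0.52 | 206 | 260 | 865 | 31 |

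The last column holds heart rate fixed between baseline and follow-up.

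**Can the 450 ms limit be reached?** At 120 bpm, W = 450 ms needs a raw QT of 450 / 0.5^(1/3) = 567 ms, longer than the 500 ms between beats. In general QT would have to exceed RR once RR^(4/3) < 0.45, that is RR < 0.549 s, or above about 109 bpm.

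**How often would it trigger?** The reference distribution is taken as normal, which is a convenience because the highest observed value was 444 ms. Then P(F ≥ 450) is about 4.2%. For the written value the probability is about 1 in a million at 80 bpm and effectively zero from 100 bpm. If the true mean were 470 ms, 74% of readings should be flagged. The written formula would flag 0.8% at 80 bpm and about 1 in 10 million at 100 bpm.

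**Sensitivity to heart rate.** Hold the Fridericia value at 400 ms and let heart rate fall from 140 to 120 bpm. The written value goes from 400 × 0.5685 = 227.4 to 400 × 0.6300 = 252.0. This is an apparent rise of 24.6 ms with no true change, against the 20 ms that the sub-study is sized to detect. The reverse change in heart rate would hide a rise of the same size.

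**Unit of RR.** With RR in milliseconds, a raw QT of 300 ms at 120 bpm gives 300 × 500^(1/3) = 2381 ms. Seconds is therefore the only workable reading.

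**The case against.** The operative instruction is the named method, and the bracket only glosses it. ECG software or a trained reader would probably apply the standard formula, in which case the damage stays in the text. Literal use should also look odd. At 120 bpm the reference mean would be recorded as 249 ms, below the whole reference range, and ECGs go to two centres for quality control. These points stand, and they make prolonged undetected use less likely. They do not make the written definition right.

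A reader might go further in three ways that the protocol does not support:
- **That every QTc in the sub-study is too low.** This requires that the bracket was actually applied, with RR in seconds. Nothing in the protocol shows that, and no erroneous QTc value is presented.
- **That harmful prolongation would be invisible.** The grade 3 rise criterion still operates, though weakened. Grade 4 rests on clinical consequences, and section 8.5.4 lists arrhythmias, ischaemia and heart failure separately at randomisation.
- **That the comparison of courses 1 and 3 is confounded because heart rate falls as anaemia recovers.** The protocol gives no heart-rate trend, and children must be clinically stable at randomisation. The 33 concurrent placebo children partly guard against a trend common to both arms. The 25 ms figure shows sensitivity to heart rate, not an expected bias.

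**Conclusion.** The contradiction is real, and nothing in the protocol corrects it: section 9.6.1 names one correction and writes its inverse. The consequence is conditional. If the bracket is applied literally with RR in seconds, QTc is recorded at 0.83 to 0.52 of the Fridericia value over 80 to 160 bpm. The absolute 450/470/500 ms limits would then almost never trigger. A true 60 ms rise would be recorded as 50 to 31 ms at a fixed heart rate, and a change in heart rate alone could shift QTc by more than the design difference.

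The ratio itself is algebra. Its size depends on the assumed heart rates, and the trigger frequencies also depend on normality and on the reference values being on the Fridericia scale. Whether any recorded value is wrong cannot be told from the protocol. The text must still be corrected, because it is the only definition behind rules on exclusion, withholding and continuation in young children.

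**What to change.** 1. Amend section 9.6.1 to read QTc = QT divided by the cube root of RR, with RR in seconds.
2. Confirm in writing which formula the site readers, the ECG software and the analysis dataset used.
3. If the written formula was used anywhere, recompute QTc, the grades and the comparison of course 1 with course 3 from the stored QT and RR before the DMEC relies on them.

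The thresholds and the clinical rules attached to them stay as they are, and so does the sample size. The cost is a one-line amendment and a check of the derivation, plus a re-run if the check fails. No new data are needed.

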### 8.10.2. Blinding

Neither the caretakers, study staff, nor investigators will know which arm a child is in. Thus the treatment group may only be determined by comparing the child's study id to the blinded list of envelope/box numbers. The master code to randomisation code will be kept in a sealed envelope. Only the study pharmacist (on site), and the trial statistician and the DMEC statistician (both off-site) will have access to master-code until the study is completed or stopping rules are reached and unblinding is required. The randomisation scheme will also be available to the principal site investigator and the study safety monitor, but only as individual treatment code envelopes, indicating the treatment for each randomised subject. The international collaborators, clinical monitors, or other personnel from any Contract Research Organization (CRO) handling the data on behalf of the sponsor, will have no access to the randomisation scheme. The treatment allocations will be disclosed after the data is locked and a statistical analysis plan has been submitted to the DMEC.

All laboratory tests will be conducted by subject study number, date of birth and date of sample. Laboratory personnel will be unaware of the randomisation group of the subject. The study statistician conducting the interim analysis will remain blinded throughout the analysis.

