#### 9.5.1.2. Interim analyses and criteria for termination of the trial

An interim analysis will be conducted on the primary endpoint when 50% of participants have completed the 6 months follow-up. The interim-analysis will be performed by an independent statistician, blinded for the treatment allocation. The statistician will report to the independent DMEC. The DMEC will have unblinded access to all data and will discuss or report the results of the interim-analysis with the Trial Steering Committee (TSC), e.g. in a joint meeting. The TSC decides on the continuation of the trial and will report to the ethics committees.

The Lan-DeMets spending function with O'Brien-Fleming type boundaries will be employed and the sample size inflated (see 8.8.1, page 40) to preserve the overall one-sided type I error rate for efficacy at the  $\alpha=0.05$  level at the final analysis. If the stopping boundary is crossed at the interim analysis and the RR is less than 1, i.e. the observed incidence rate in the PMC arm is less than the expected incidence rate under the null hypothesis, it will be concluded that the study has demonstrated that the efficacy of PMC is superior to that of placebo in the prevention of death or all-cause readmission. The trial recruitment can then be stopped unless the DMEC advises otherwise. Statistics will not be the sole basis for the decision to stop or continue and the DMEC can advise to continue recruiting in the trial, or stop recruiting but continue to complete the intervention as per randomization in the remaining active children, even if statistically the stopping boundary is crossed, e.g. in order to continue collecting more safety information or data for further sub-group analyses etc. The trial will not be stopped in case of futility, unless the DMEC during the course of safety monitoring advises otherwise.

A detailed plan for interim analysis, the provisional stopping rules and how the stopping rules will be applied, will be drawn up prior to the start of the interim analysis and documented in the study statistical analysis plan.

In addition, regular review of the quality of the study data will be conducted at each meeting of the DMEC.

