##### *Trial members*

- The Chief Investigator and all Country Co-Principal Investigators.
- Other co-investigators and the trial statistician will attend the meetings if and when required.

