#### 16.3.2.5. Frequency of Meetings

The TSC shall have an initial face to face start up meeting to discuss the protocol and establish the DMEC. A second meeting shall take place before the initiation of the trial to finalise the protocol and approve the commencement of the trial. Thereafter the TSC will normally meet once a year in the life span of the trial and one meeting at the closure of the trial.

The Chair and at least 2 of the three independent members together with the CI and trial co-ordinator shall constitute the quorum. If so required, in addition a member of the funder can be invited to attend the meetings.

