#### 16.3.3.2. Role DMEC

The DMEC consist of 3-4 members (including one or more clinicians and one statisticians, all with experience in clinical trials).

The DMEC shall assess the data regularly (before the annual TSC meeting) to review the data and the interim analysis. The assessment could be via email or other electronic medium annually prior to the TSC meeting. In the first year of recruitment more frequent assessment (bi-annually) is recommended for this trial with one face to face meeting at least once during the trial.

The members should be the only personnel to see the results separated by treatment group during the trial. They are independent and look at the trial from an ethical point of view of the participant safety, future patients and society in general. It is their responsibility to prevent patients being exposed to any excess risks by recommending to the Trial Steering Committee (TSC) for the trial suspension or termination early if the safety or efficacy results are sufficiently convincing. The trial statistician is usually invited to attend part of the DMEC meeting to present the most current data from the trial. This will be blinded, unless the DMEC specifically requests for an unblinded analysis.

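### Both stopping procedures send interim results to a steering committee that includes the chief and country investigators, in conflict with the rule that results by arm stay within the DMEC

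*Protocol*

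**What the plan says.** **Cardiac rule, Protocol 9.6.1.** A statistician who does not know the allocation analyses the completed sub-study and reports to the DMEC. Then: "The DMEC will have a meeting during which they will have access to the unblinded data". Two branches follow. Without a clinically relevant increase, "they will inform the Trial Steering Committee (TSC) for the study to continue as per the approved protocol". If the prolongation grows from course to course, the rule is different: "the DMEC will share the results of the interim-analysis with the Trial Steering Committee (TSC) in a joint meeting". Whether the trial continues is then for the TSC to decide, and it may suggest amendments.

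**Efficacy interim, Protocol 9.5.1.2.** The DMEC sees all data unblinded. It then "will discuss or report the results of the interim-analysis with the Trial Steering Committee (TSC), e.g. in a joint meeting". This does not depend on what the results show. The TSC again decides on continuation.

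**Who sits on the TSC, Protocol 16.3.2.** The trial members include "The Chief Investigator and all Country Co-Principal Investigators". On validity of meetings, 16.3.2.5 says: "The Chair and at least 2 of the three independent members together with the CI and trial co-ordinator shall constitute the quorum".

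**Who may see results by arm.** On the DMEC, 16.3.3.2 says: "The members should be the only personnel to see the results separated by treatment group during the trial". Section 16.3.3.3 describes what the DMEC sends to the TSC as reports and recommendations, and treats release of interim data as something to be considered on request.

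**Blinding, Protocol 8.10.2.** "Neither the caretakers, study staff, nor investigators will know which arm a child is in".

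**The concern.** The two stopping procedures and the DMEC terms of reference give different answers to one question: what leaves the DMEC after an unblinded look? The terms of reference keep results by arm inside the DMEC. The stopping procedures pass results on to a committee on which the people running the trial sit.

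This matters because the trial need not stop afterwards. Section 9.6.1 foresees continuation with an amended protocol. Section 9.5.1.2 lets the DMEC advise continued recruitment, or completion of the intervention in active children, even if the efficacy boundary is crossed. Investigators could then be running a double-blind trial while knowing how the arms compare. All-cause readmission, part of the primary endpoint, involves clinical judgement, and under 9.6.3 the study clinician assigns SAE causality. Such knowledge cannot be withdrawn once given.

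**Working it through.** No arithmetic applies to the core point. It rests on setting the sections side by side.

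1. *What the DMEC holds.* Unblinded data in both procedures (9.5.1.2 and 9.6.1).
2. *What it passes on.* The results of the analysis, in both procedures. In 9.6.1 this is clearly more than a recommendation: the branch without a signal only tells the TSC to carry on, while the branch with a signal shares results. The protocol itself separates the two.
3. *Who receives it.* The TSC, whose trial members include the chief investigator and every country co-principal investigator (16.3.2). Section 16.3.2.3 says that most TSC members are independent of the trial management group. That does not remove the investigators.
4. *Can they be left out?* Not under the quorum rule as written, since 16.3.2.5 counts the chief investigator and the trial co-ordinator. No closed session is described in the text at hand. Some text next to the committee membership lists is withheld from this copy, so that absence is established only for what can be read.
5. *What is allowed.* Under 16.3.3.2, only DMEC members should see results by arm. The rule turns on separation by arm, so results labelled A and B would conflict with it as well as results with the arms named. Only pooled figures or a bare recommendation would comply, and neither 9.5.1.2 nor 9.6.1 specifies either.
6. *Could it travel further?* Under 16.3.2.6 each TSC meeting produces a summary of findings and recommendations that goes to the funder, the sponsor and the trial management group. Section 16.3.1.2 puts site clinicians in that group. Nothing says that the summary must omit results by arm.
7. *Are the triggers live?* The cardiac rule needs a signal. For the efficacy interim, 8.8.1.1 says that a blinded sample size re-estimation was preferred to an interim analysis. However, 9.2.5.1 and 9.5.1.2 still prescribe the interim, so the instruction stands in the current text.

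**The case against.** The other side has several good points.

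- *The text does not say that unblinded results are shared.* A reader might take 9.5.1.2 and 9.6.1 as ordering disclosure by named arm. They mention only the results of the analysis, prepared by a statistician who does not know the allocation. Disclosure by arm is an inference. It is a strong one, because the DMEC is unblinded immediately beforehand, the sub-study has 33 children in each of two arms, and the TSC must decide on the basis of what it is given. It remains an inference all the same.
- *Section 8.10.2 is not directly breached.* A reader might infer that it is. Its sentence concerns which arm an individual child is in, whereas a committee would see aggregate results. The direct conflict is with 16.3.3.2.
- *Controlled release is foreseen.* Section 16.3.3.3 lets the DMEC consider requests for interim data, and 16.3.3.2 is worded as a recommendation. This softens the conflict but does not remove it: a standing instruction to share is not a request considered case by case.
- *A quorum does not forbid a closed part of a meeting.* That is true, but none is provided for, and any decision taken without the chief investigator would not be quorate.
- *The cardiac route to bias is narrow.* A reader might infer that most of the 1040 children are exposed, or that ECG readers could work out allocation. The analysis comes after the sub-study is complete, so its planned ECGs have already been read. The sub-study covers 66 / 1040 = 6.3% of children, and QTc results reveal nothing about readmissions. As an illustration, assume a between-arm shift of 20 ms and an SD of 31 ms (figures borrowed from 8.8.2, where they describe a change between courses), normal readings and a midpoint cut. The best guess from one reading is then right with probability Φ(10 / 31) = Φ(0.32) ≈ 0.63, against 0.50 by chance.
- *The sub-study may be over.* It was planned for early in the trial. First enrolment was in May 2016 and this version is dated February 2018, about 21 months into a planned 24-month recruitment. The protocol does not say whether the cardiac analysis has been done.

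There is also a fair governance argument: the body that decides on continuation after a safety signal may reasonably want to see data. That supports giving data to its independent members. It does not explain why investigators should see them when 16.3.3.2 says otherwise.

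**Conclusion.** The conflict is real and stands in the current text. As written, 9.5.1.2 and 9.6.1 direct interim results to a committee that includes the chief and country investigators, without limiting them to pooled figures or a recommendation, while 16.3.3.2 reserves results by arm to DMEC members. Because the trial may continue after disclosure, this is an avoidable risk of operational bias in a double-blind trial.

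The size of any bias cannot be computed from the protocol. Exposure is conditional: it arises in the cardiac branch only if a signal is found, and in the efficacy branch only if the interim, possibly superseded, is still carried out. The conclusion assumes that the shared results would be separated by arm, which is the natural reading but is not stated. On that footing the passages should be reconciled. The point does not invalidate the design.

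**What to change.** Reconcile 9.5.1.2, 9.6.1, 16.3.2.5 and 16.3.3.2 as follows.

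- In 9.5.1.2 and 9.6.1, the DMEC sends the TSC a recommendation to continue, modify or stop, without results by arm.
- If the TSC needs data to decide, only its independent members see them, in a closed session.
- Amend the quorum in 16.3.2.5 so that such a session is valid without the chief investigator and the trial co-ordinator.
- State in 16.3.2.6 that the TSC summary to the trial management group contains no results by arm.
- State whether the efficacy interim in 9.2.5.1 and 9.5.1.2 still applies after the re-estimation in 8.8.1.1. If it does not, delete it.

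The cost is a few sentences in the protocol and the terms of reference. The TSC keeps its decision role and no clinical rule changes. The downside is that investigator members would take part in a decision on continuation without seeing data by arm.
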